### Sample size

The trial is powered to detect significant differences relevant to the primary outcome. A power analysis (G-power 3.1) for medium effect (Cohen’s d = .5) was conducted with power of .08, and using the conventional significance level (.05), resulting in a desired sample of 102 (51 participants in each group). Consistent with previous studies (e.g. [75]) allowing for a conservatively estimated attrition rate of 20% to follow up, a sample of 120 will be recruited. Based on the projected sample size of 102, power of 0.8, and zero, small, medium or large effect sizes conditions for the indirect effect, the mediation analyses are well-powered to detect a medium beta paths between the independent variable and the mediator and between the mediator and the dependent variable (β = .0.39) using bootstrapping and the Sobel test [76]. Data will be collected using online self-report measures with the Qualtrics platform at the four measurement points; baseline, mid-intervention, post-intervention, and 6-months follow-up.

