This is consistent with the CONSORT standard [78]. If data are non-normal, then it will be analyzed using generalized linear MMRM. The mediational impact of pre to post MAIA, MSES, EQ and NAS will be assessed using the Sobel test, a method for measuring indirect effects [79]. The test assesses the significance of the product of the coefficients for treatment-mediator and mediator-outcome effects. A bootstrapped multivariate extension of the Sobel test will be used to examine both the total indirect effect and the individual effect and the effect of each mediator. The first model will comprise: group (MiCBT vs wait-list control) as the independent variable; clinical DASS-21 and K10 measures as the dependent variables; and MAIA (interoceptive awareness), EQ (metacognitive awareness), MSES-R (Emotion Regulation, Distress Tolerance, Equanimity subscales and total) and NAS (equanimity), scales that reveal significant group x time interactions, as mediators. Two time-frames will be tested for changes over the course of the program itself (mediators measured at 4 weeks; outcomes at 8 weeks) and in the longer term (mediators measured at 8 weeks, outcomes at 6 months). The second model will comprise: group (MiCBT vs wait-list control) as the independent variable: psychological wellbeing SWLS and FS measures (measured at 6 months) as the dependent variables; and MSES-R subscales of Taking Responsibility, Social Skills, Interpersonal Effectiveness and total score (measured at 8 weeks), MAIA (interoceptive awareness), EQ (metacognitive awareness), MSES-R (Emotion Regulation, Distress Tolerance, Equanimity subscales and total) and NAS (equanimity) scales that reveal significant group x time interactions, as mediators.

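### The Sobel test and a bootstrap are both named for the same indirect effects with neither given precedence; Sobel is the conservative one, so the planned bootstrap interval should be named as the deciding criterion

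*Protocol article*

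**What the plan says.** In the Statistical analysis section, the mediating effect of four scales (MAIA, MSES, EQ, NAS) "will be assessed using the Sobel test, a method for measuring indirect effects". The section explains the test this way: "The test assesses the significance of the product of the coefficients for treatment-mediator and mediator-outcome effects". It continues: "A bootstrapped multivariate extension of the Sobel test will be used to examine both the total indirect effect and the individual effect", and the same sentence extends this to each mediator. Two models follow. Each has several candidate mediators, and only scales with a significant group-by-time interaction are admitted.

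The Sample size section takes the mediation analyses to be adequately powered for medium paths of 0.39 (printed with a stray point), "using bootstrapping and the Sobel test". Its basis is given as "Based on the projected sample size of 102, power of 0.8, and zero, small, medium or large effect sizes conditions".

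Neither section says which of the two procedures settles whether a scale is a mediator.

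**The concern.** The null hypothesis is that the product of the treatment-to-mediator path (a) and the mediator-to-outcome path (b) is zero. The Sobel statistic treats the estimated product as normal. That is a fair approximation only when at least one path is large relative to its standard error. Otherwise the test is conservative, and it can miss an indirect effect that a bootstrap of the same data would detect.

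Mechanisms of action are the stated secondary aim (Aims and hypotheses). The Methods/design section also leans on the mediation analyses to separate specific from general therapy effects, because there is no active control. With several mediators, four outcome scales, two time-frames and an analysis that is not blinded (Blindness section), the plan should fix the deciding test in advance.

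**Working it through.** **Inputs.** From the Sample size section: n = 102 in two arms of 51, both paths 0.39, target power 0.8, and a 5% level ("using the conventional significance level (.05"). Sidedness is not stated; two-sided is assumed here. Also assumed: one mediator, no direct effect, unit residual variances, and group coded -1/+1. Path sizes other than 0.39 are assumptions.

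**Model and tests.** M = aX + e1 and Y = bM + e2, with Y regressed on X and M.
- Sobel: z = ab / sqrt(a²·se_b² + b²·se_a²), reject if |z| > 1.96.
- Percentile bootstrap: 1,000 resamples, reject if the 95% interval for ab excludes 0.

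**Why Sobel is conservative.** Dividing through by se_a·se_b gives z = z_a·z_b / sqrt(z_a² + z_b²), which is always smaller in size than the smaller of the two path statistics.
- Both paths zero: for independent standard normal z_a and z_b, this ratio is normal with standard deviation 1/2. Rejection needs a standard normal beyond 2 × 1.96 = 3.92, a probability below 0.01%.
- a = 0, b = 0.39: z_b is about 0.39 × √102 = 3.94, with square 15.5. Holding z_b there, rejection needs z_a² > 3.84 × 15.5 / (15.5 − 3.84) = 5.1, so |z_a| > 2.26, a probability of about 2.4%.
- a = 0, b = 0.59: z_b is about 5.96, with square 35.5. Rejection needs z_a² > 3.84 × 35.5 / (35.5 − 3.84) = 4.31, so |z_a| > 2.07, a probability of about 3.8%.

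**The plan's own figure.** At paths 0.39/0.39 and n = 102, Sobel power is 88.4% and percentile bootstrap power 93.9%, so the stated 0.8 is met by both. Sobel passes 80% between n = 88 (79.8%) and n = 90 (80.6%). With 120 × 0.8 = 96 participants, power is 83.7% and 90.3%.

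**Rejection rates, n = 102, 10,000 trials per row:**

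| a / b | Sobel | Percentile bootstrap | Gap (points) |
|---|---|---|---|
| 0 / 0 | 0.0% | 0.2% | – |
| 0 / 0.39 | 2.3% | 4.8% | – |
| 0 / 0.59 | 3.7% | 5.2% | – |
| 0.25 / 0.25 | 26.2% | 46.3% | 20.1 |
| 0.26 / 0.26 | 30.7% | 51.1% | 20.4 |
| 0.30 / 0.30 | 52.0% | 70.2% | 18.2 |
| 0.36 / 0.36 | 79.3% | 88.6% | 9.3 |
| 0.39 / 0.39 | 88.4% | 93.9% | 5.5 |

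The null rows agree with the hand calculation. A group difference of d = 0.5 on the mediator equals a = 0.25 on this coding (0.5 / 2). With 4,000 trials, that gives 53.4% v 68.9% at b = 0.39 (15.5 points; a separate run gave 55% v 68%, 13 points) and 27.8% v 49.4% at b = 0.26 (21.6 points, the largest gap found).

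**How often the two tests conflict (3,000 trials):**
- 0.39/0.39: 87.9% v 93.4%, disagreement in 5.8% of trials.
- 0.25/0.39: 53.6% v 69.0%, disagreement in 15.5% (13% in the separate run).
- 0.25/0.26: 27.9% v 50.4%, disagreement in 22.6%.

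The power differences are 5.5, 15.4 and 22.5 points, almost equal to the disagreement rates. So nearly every conflict is a positive bootstrap beside a negative Sobel test.

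**Scale of the 0.39 path.** The article does not say what 0.39 means for a two-level group. If it is a group difference of 0.39 residual standard deviations (0/1 coding), power is 33.3% (Sobel) and 46.4% (percentile bootstrap), a gap of about 13 points, and neither test reaches 0.8.

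**The case against.** The strongest reply is that the bootstrap is already planned for the total and each separate indirect effect. On this reading the Sobel sentences merely introduce the product-of-coefficients idea and the bootstrap sentence gives its implementation. Precedence between named methods is also something a SAP may settle, and none is shown. This carries weight. A reader might infer that mediation will be judged by Sobel alone, so that true mediators will be lost; the documents do not support that, because nothing says Sobel overrides the bootstrap. The reply does not remove the point, however. The article does state Sobel as the method of assessment, and it rests the power claim on both tests.

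A reader might also take about 22 points as the trial's loss of power. The documents do not support that either: it arises at assumed paths near 0.25 to 0.26. At the protocol's own 0.39 the loss is 5 to 6 points on -1/+1 coding, and the stated power is met.

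Nor is rejection near 0% peculiar to Sobel. With both paths zero the percentile bootstrap rejects in only 0.2% of trials, and with one large path Sobel is close to nominal at 3.7%.

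Finally, the simulation has one mediator and no selection step, whereas the plan has several mediators and screens them. The figures illustrate the two tests; they are not this trial's operating characteristics.

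**Conclusion.** The point holds as a minor one. Two tests that can disagree are named for the same indirect effects, and the one named first is the less powerful. Sobel rejects in about 0% to 4% of null trials. It gives up 5 to 6 points of power at the protocol's medium paths, and about 13 to 22 points at smaller, assumed paths. The tests conflict in about 6% to just over 22% of trials. These sizes rest on n = 102, a two-sided 5% level, a single mediator, no direct effect and -1/+1 coding of group.

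The error is conservative: Sobel does not create false claims of mediation. It bears on the secondary, mechanistic aim and leaves the primary comparison untouched. The mediation power statement is not shown to be wrong; whether it holds depends on the scale of the 0.39 path, which the article does not give.

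**What to change.** In the Statistical analysis section, state that each indirect effect, total and separate, is judged by whether its 95% percentile bootstrap confidence interval excludes zero. Report the Sobel p-value as descriptive or drop it. Name the interval type: in the same simulation a bias-corrected interval rejected in 7.7% of trials under the 0/0.39 null, against 4.8% for the percentile interval.

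In the Sample size section, refer the mediation power statement to the bootstrap only. On -1/+1 coding the 0.8 claim stands without change; a few words on what 0.39 means for a two-group variable would make it checkable.

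The cost is wording only. A bootstrap is already planned, and no data, visits or sample size change.

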#### Mindfulness-based Self-Efficacy Scale-Revised (MSES–R)

This 22-item self-report measure is designed to assess the changes in levels of perceived self-efficacy before, during and after mindfulness-based therapy [32]. There are six subscales, Emotion Regulation, Distress Tolerance, Equanimity (considered here as measuring aspects of equanimity), Taking Responsibility, Social Skills, and Interpersonal Effectiveness (considered here as measuring aspects of interpersonal skills). Items are rated on a 5-point Likert scale from 0 (*not at all*) to 4 (*completely*). Higher scores indicate higher mindfulness based self-efficacy. Subscales can be used separately to assist in identifying relative strengths and weaknesses or combined to provide a global score. The MSES-R total shows high internal consistency (Cronbach’s alpha .86) [32]; has a good divergent validity, inverse relationships with the DASS-21 [60], and good concurrent validity with the Freiberg Mindfulness Inventory (FMI) [61], the Mindfulness Attention and Awareness Scale (MAAS), [62], the Kentucky Inventory of Mindfulness (KIMS), [63, 64] and the Five Factor Mindfulness Questionnaire (FFMQ), [65, 66].

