### Mediator hypotheses

It is hypothesized that the mediators of the clinical change will be reflected by changes in equanimity (NAS), decentering (EQ), interoceptive awareness (MAIA) and Mindfulness-based self-efficacy (MSES-R). The following mediation hypotheses will be tested: 1) improvements in the DASS-21 and K10 (clinical symptoms) at the end of MiCBT treatment will be mediated by improvements in the MSES-R (equanimity-related subscales), EQ and NAS mid-intervention; 2) improvements in clinical symptoms (DASS-21 and K10) at the six-month follow-up will be mediated by improvements in the MSES-R (equanimity-related subscales), EQ and NAS at the end of treatment. We will also explore the degree to which 3) improvements in the SWLS and FS at the six-month follow up is mediated by improvements in the MSES-R (interpersonal skills and social skills subscales) compared to MSES (equanimity subscales), EQ and MAIA measured at the end of treatment.

Measurements of ethical awareness and compassion as addressed in stage 4 of the program were not included as they would make the number of items unmanageable but could be considered in future studies and their target is relapse prevention which not the focus of this study.

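### The mediation hypotheses concern improvement, but the models list no baseline term and do not fix how improvement enters them

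*Protocol article*

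**What the plan says.** The Mediator hypotheses section of the protocol article frames both sides of the mediation as improvement. Symptom improvement at the end of treatment "will be mediated by improvements in the MSES-R (equanimity-related subscales), EQ and NAS mid-intervention". For the longer term, "improvements in clinical symptoms (DASS-21 and K10) at the six-month follow-up will be mediated by improvements in the MSES-R" (and the EQ and NAS) at the end of treatment.

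The Statistical analysis section describes the models in three ways:

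- A general sentence: "The mediational impact of pre to post MAIA, MSES, EQ and NAS will be assessed using the Sobel test".
- The model terms: "The first model will comprise: group (MiCBT vs wait-list control) as the independent variable; clinical DASS-21 and K10 measures as the dependent variables", with the mediator scales as mediators. Only scales with a significant group-by-time interaction are admitted.
- The timing: "Two time-frames will be tested for changes over the course of the program itself". For this first time-frame the scores are dated as "mediators measured at 4 weeks; outcomes at 8 weeks". The second time-frame, which looks at lasting effects, has "mediators measured at 8 weeks, outcomes at 6 months".

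No baseline mediator, baseline outcome or other covariate is named. Baseline values will exist, because baseline is one of the four planned measurement points and both arms complete all measures at each point.

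**The concern.** The section can be read in at least two ways, and they give different estimands. Under one, the mediator is the score at 4 weeks and the outcome is the score at 8 weeks. Under the other, the mediator is a change from before to after the program. For the 8-week outcome that second reading cannot be right as worded: a change ending at week 8 does not precede an outcome measured at week 8, and it contradicts the 4-week mediator in the same section.

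The choice matters because the indirect effect is the product of two paths and randomization protects only the first, from group to mediator. The path from mediator to outcome is observational. If habitually more equanimous people are habitually less distressed, later scores of the two correlate within each arm even when gaining equanimity does nothing to symptoms. Without a baseline term, that correlation goes straight into the mediator-outcome coefficient. The rule that admits only scales with a significant group-by-time interaction ensures that the first path tends to be non-zero.

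Mechanism is the stated secondary aim. The Methods/design section also relies on the mediation analyses to separate specific from general therapy effects, because there is no active control.

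**Working it through.** **Sample size used.** The plan's figure is 102 (51 per group) for d = 0.5 at the 0.05 level, reading the printed power of .08 as the 0.8 given later in the same section. A one-sided two-sample t test reproduces it exactly: 51 per arm, power 0.806. A two-sided test needs 64 per arm. The check uses 51 per arm because that is the plan's number; the point does not depend on it.

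**Assumptions (not in the documents).** There is no true mediation. The group effect is a = 0.5 SD on the mediator and 0.5 SD on the outcome. The mediator-symptom correlation is r and the baseline-to-later stability is s. Two data models were used, since the documents favour neither:

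- Model A (autoregressive): baseline scores correlate r; each later score = s × its own baseline + group effect + independent error.
- Model B (stable trait): each score = a stable part (share s of the variance) + independent occasion error; r is the correlation between the stable parts.

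**Expected mediator-outcome slope within arm (truth = 0).**

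- Later scores, no baseline: A gives s²r; B gives s·r.
- Change scores: A gives (1 − s)r/2; B gives 0.
- Baseline mediator and outcome as covariates: A gives 0; B leaves a small remainder, because one noisy baseline does not fully capture the stable part.

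**Central case, r = −0.5, s = 0.7.** The spurious indirect effect is slope × 0.5, and its share is that product divided by the 0.5 SD total effect.

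| Analysis | Model | Slope | Indirect effect (SD) | Share | Simulated indirect effect |
|---|---|---|---|---|---|
| Later scores | A | 0.49 × (−0.5) = −0.245 | −0.1225 | 24.5% | −0.121 |
| Later scores | B | 0.7 × (−0.5) = −0.35 | −0.175 | 35% | −0.171 |
| Change scores | A | 0.3 × (−0.5)/2 = −0.075 | −0.0375 | 7.5% | −0.039 |
| Change scores | B | 0 | 0 | 0% | 0.001 |
| Baseline-adjusted | A | 0 | 0 | 0% | −0.001 |
| Baseline-adjusted | B | (simulated only) | | 0.033/0.5 = 6.6% | −0.033 |

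**False-positive rates, nominal 5%, one mediator.**

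- Model A, central case (bootstrap-type interval; Sobel in brackets): later scores 47% (26%), change scores 11% (5%), baseline-adjusted 5% (2%).
- Model A, r −0.3 to −0.7 and s 0.5 to 0.7, bootstrap-type: later scores 8% to 66%, change scores 6% to 29%, baseline-adjusted 3% to 5%.
- Model B, Sobel: 50% with later scores in the central case. Over r −0.35 to −0.6, s 0.6 to 0.85 and mediator effects of 0.5 to 0.8 SD: later scores 20% to 97%, change scores 1% to 4%, baseline-adjusted 3% to 15%.
- A further simulation at 51 per arm: later scores about 16% to 64%, change scores 3% to 22% depending on the data model, baseline-adjusted about 3% to 10%. With four mediators, later scores gave 32% to 81% for the total indirect effect.

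**Two conditions on the result.** With no group effect on the mediator (Model A, central r and s), the later-score model rejects in only 4% of runs. Restricting Model A to runs where the group effect on the mediator is significant, a stand-in for the plan's entry rule, raises the later-score range to between 11% and 94%.

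**The case against.** The strongest reply is that the plan may never intend raw scores. Two sentences use change language ("The mediational impact of pre to post MAIA, MSES, EQ and NAS will be assessed using the Sobel test" and "Two time-frames will be tested for changes over the course of the program itself"), and the 4-week and 8-week labels could simply date the end of a change. A reader might infer that the models certainly use later scores without baseline; the text does not establish that. What stands is that it does not establish the alternative either: nowhere does it say whether improvement enters as a change score or through a baseline covariate.

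It would also be too strong to say that the pre-to-post wording never fits. For the 6-month outcomes, a mediator change from before treatment to week 8 is what the hypotheses describe, and it precedes the outcome. The clash is confined to the 8-week outcome.

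A covariate list is often left to a fuller document. That would answer a bare omission. Here the article itself fixes the test, the model terms and the time points, and these do not agree with one another.

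The size of the bias is open to challenge, and fairly so. The documents give neither the correlations nor the stabilities. The MSES-R description reports "inverse relationships with the DASS-21" as validity evidence, which makes a correlation plausible, but it does not say that this was observed before treatment and gives no value. The plan also foresees several mediators together. With four intercorrelated mediators (0.5 to 0.6, assumed) in the stable-trait central case, the rate for an individual mediator fell to 9% to 13%. That relief does not extend to the total indirect effect, which the plan also tests.

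**Conclusion.** The point holds as a defect of specification with a real risk of bias. The hypotheses concern improvement; the analysis section does not fix how improvement is represented, lists no baseline term, and contradicts itself on the mediator for the 8-week outcome.

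Applied literally, and provided MiCBT moves the mediator, the listed models would report false mediation in roughly 15% to 65% of trials for one mediator with a bootstrap-type test. This assumes correlations of −0.35 to −0.5, stability of 0.6 to 0.7 and a 0.5 SD effect on the mediator. The Sobel test gives lower rates in the same setting, and weaker correlation or stability lowers both (8% by bootstrap and 3% by Sobel at r = −0.3, s = 0.5 in Model A). Change scores alone help, but how much depends on the data model.

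Two stronger conclusions should not be drawn. Between-person correlation alone does not produce a mediation finding; a group effect on the mediator is needed too. And the primary treatment comparison is untouched: this concerns the secondary mechanism aim.

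**What to change.** In the Statistical analysis section:

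1. Define the mediator as the 4-week score for the 8-week outcome and the 8-week score for the 6-month outcome.
2. Include the pre-treatment value of each mediator in the model, and of the outcome, as covariates in both the group-to-mediator and the mediator-to-outcome regressions.
3. Report the change-score version as a sensitivity analysis. The two approaches fail under different data models, so agreement between them is informative.
4. Reconcile the pre-to-post wording with the 4-week mediator. It can stay for the 6-month models.

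The cost is analysis wording plus one baseline term per mediator and one for the outcome. The first model lists up to seven mediators (MAIA, EQ, NAS, three MSES-R subscales and the MSES-R total), so the full version needs up to 7 + 1 = 8 extra terms at n = 102. No new data are needed. Baseline adjustment may leave a small residual bias if single baseline scores are noisy.

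### The second mediation model lists all six MSES-R subscales with their total, both models screen mediators on significance, and the mediator lists disagree between sections

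*Protocol article*

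**What the plan says.** **The scale.** The section on the MSES-R describes its structure: "There are six subscales, Emotion Regulation, Distress Tolerance, Equanimity", followed by Taking Responsibility, Social Skills and Interpersonal Effectiveness. It adds: "Subscales can be used separately to assist in identifying relative strengths and weaknesses or combined to provide a global score".

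**The models.** The Statistical analysis section specifies joint models: "A bootstrapped multivariate extension of the Sobel test will be used to examine both the total indirect effect and the individual effect", and also the effect of each mediator.
- Model 1 (DASS-21 and K10 as outcomes) uses MAIA, EQ and "MSES-R (Emotion Regulation, Distress Tolerance, Equanimity subscales and total) and NAS (equanimity), scales that reveal significant group x time interactions".
- Model 2 (SWLS and FS at six months) uses "MSES-R subscales of Taking Responsibility, Social Skills, Interpersonal Effectiveness and total score (measured at 8 weeks", then MAIA, EQ, "MSES-R (Emotion Regulation, Distress Tolerance, Equanimity subscales and total" and NAS, under the same significance condition.

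**The hypotheses.** In Mediator hypotheses, the first numbered statement says that gains in clinical symptoms "will be mediated by improvements in the MSES-R (equanimity-related subscales), EQ and NAS mid-intervention". The second names the same scales at end of treatment. The third, exploratory, sets the interpersonal and social-skills subscales against the equanimity subscales, EQ and MAIA.

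**The power.** The Sample size section states that at 102 participants, with power 0.8, "the mediation analyses are well-powered to detect a medium beta paths between the independent variable and the mediator" and from mediator to outcome. The path size is printed as .0.39 and is read here as 0.39.

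**The concern.** Three stated rules work against what the mediation analysis is meant to deliver.

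1. A total entered beside all of its components leaves their separate effects undefined, although the plan promises an effect for each mediator. In Model 2 the total also mixes the interpersonal and equanimity blocks that the third hypothesis wants to compare.
2. The group x time interaction on a mediator is in essence the treatment-mediator path, one of the two factors in the Sobel product. Admitting a scale only when that path is significant selects on the quantity then tested.
3. With different mediator sets in the hypotheses and the models, it is unclear which mediators were specified in advance.

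Mechanism is the trial's secondary aim. The Methods/design section also relies on the mediation analyses to address, to some extent, specific versus general therapy effects, because there is no active control. A reader who takes the power statement to cover the joint models could also over-read a null result for a single scale.

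**Working it through.** **Rank of the mediator-outcome regression.** Assumption: the total is a sum or mean of the subscales, T = S1 + … + S6 up to scaling. MAIA, EQ and NAS play no part in the dependence and are left out.

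| Columns | Number | Rank |
|---|---|---|
| Intercept, group, six subscales, total (Model 2) | 9 | 8 |
| Intercept, group, five subscales, total | 8 | 8 |
| Intercept, group, three subscales, total (Model 1) | 6 | 6 |

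Model 2 is singular if all seven MSES-R scores enter. The total indirect effect survives, since dropping a redundant column leaves the fit unchanged. The separate MSES-R effects do not survive.

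Model 1 is estimable but hard to read. Substituting for T,

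b1·S1 + b2·S2 + b3·S3 + bT·T = (b1 + bT)·S1 + (b2 + bT)·S2 + (b3 + bT)·S3 + bT·(S4 + S5 + S6).

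The total's coefficient is therefore that of the three subscales not listed, and each subscale's coefficient is a difference from it.

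**Effect of the screen.** Take the estimated mediator difference as N(d, SE²) and admit the scale if the estimate exceeds 1.96·SE. With c = 1.96 − d/SE, the pass rate is 1 − Φ(c), and the mean estimate among scales that pass is d + SE·φ(c)/[1 − Φ(c)].

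- Setting A: 120 × 0.8 = 96, or 48 per arm; SE = √(2/48) = 0.204.
- Setting B (assumed): 56 per arm, change scores, pre-post correlation 0.6; SE = √(2/56) × √(2 × 0.4) = 0.169.

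Example, A with d = 0.3: c = 1.96 − 1.47 = 0.49; pass rate 0.31; mean 0.3 + 0.204 × 0.354/0.312 = 0.53; ratio 1.8.

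| True d | A: passes | A: overstated | B: passes | B: overstated |
|---|---|---|---|---|
| 0.3 | 31% | 1.8-fold | 43% | 1.5-fold |
| 0.4 | 50% | 1.4-fold | 66% | 1.2-fold |
| 0.5 | 69% | 1.2-fold | 84% | 1.1-fold |

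These figures treat the screen and the path as the same estimate. If the screen is the pre-to-post interaction, that fits the week-8 mediators; for the week-4 mediators the two are related but not identical.

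**Mediator lists side by side.**

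| Scale | Hypotheses 1–2 | Model 1 | Hypothesis 3 | Model 2 |
|---|---|---|---|---|
| MAIA | no | yes | yes | yes |
| EQ | yes | yes | yes | yes |
| NAS | yes | yes | no | yes |
| MSES-R equanimity-related subscales | yes | yes | yes | yes |
| Social Skills, Interpersonal Effectiveness | no | no | yes | yes |
| Taking Responsibility | no | no | no | yes |
| MSES-R total | no | yes | no | yes |

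Aims and hypotheses, and the opening sentence of Mediator hypotheses, do name interoceptive awareness as a mediator.

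**Power.** The plan's own figure first: one mediator, both paths 0.39, N = 102, two-sided 0.05, simulated. Sobel power is 0.87 to 0.91, depending on how residual variance is scaled, and percentile-bootstrap power is about 0.93. The claim of at least 0.8 reproduces.

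For a 1:1 group variable, a standardised path r corresponds to d = 2r/√(1 − r²) = 0.78/0.921 = 0.85 in within-group SD units, or 2r = 0.78 in total SD units. The group difference on the mediator is thus about 0.8 SD.

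For one individual effect in a joint model, with a group difference of 0.78 within-group SD and b = 0.39, Sobel power is as follows. The between-mediator correlation is assumed, since the protocol gives none.

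| Mediators | 0 | 0.3 | 0.5 | 0.7 |
|---|---|---|---|---|
| 4 | 0.89 | 0.82 | 0.72 | 0.50 |
| 6 | 0.87 | 0.80 | 0.67 | 0.46 |
| 9 | 0.86 | 0.77 | 0.63 | 0.43 |

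Counting MAIA as one score, six and nine are the sizes of Models 1 and 2 without the total. For four mediators, a Monte Carlo interval standing in for the planned bootstrap gives 0.95, 0.91, 0.83 and 0.64.

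**The case against.** - **Singularity is conditional.** A reader might infer that the mediation models cannot be estimated at all. They can: Model 1 has full rank, and Model 2 fails only if all six subscales and the total pass the screen. Model 2 also serves a hypothesis that the protocol calls exploratory. This stands and limits the point. It does not rescue the list, because whether Model 2 is identified then depends on which scales happen to be significant.
- **Timing.** The Statistical analysis section opens with pre-to-post mediators, so a reader might infer that mediator and outcome lack temporal order. The same section and Mediator hypotheses both fix lagged windows (week 4 to week 8, week 8 to six months). There is no defect here.
- **Power.** A reader might infer that the claimed power is wrong, the more so as the trial plans on d = 0.5 (one mediator at that difference gives Sobel 0.54, bootstrap 0.67). The protocol ties d = 0.5 to the primary outcome, not to any mediator, and its statement reproduces on its own terms. With a bootstrap-type interval, 0.8 also holds for four mediators up to a correlation of about 0.5. What remains is that the statement does not by itself extend to individual effects in the joint models.
- **Size of the selection effect.** Setting A applies the loss expected at follow-up to earlier measurements and ignores baseline. This is fair, and it is why a range is given.
- **Lists.** MAIA and NAS are both analysed, and the Aims section supports MAIA. The mismatch is therefore a matter of reconciliation; no mechanism has been dropped from the analysis.

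**Conclusion.** The point holds in a limited form and should be fixed. It does not touch the primary treatment comparison.

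Model 2 as listed contains an exact linear dependence (rank 8 of 9), given only that the total is a linear combination of its subscales. Model 1 is estimable, with a total that overlaps its subscales. The significance screen makes both mediator lists data-dependent and overstates the path of scales that pass. The size, 1.1- to 1.8-fold for true d of 0.5 to 0.3, is illustrative and depends on the assumed numbers and precision. The numbered hypotheses and the models name different mediators.

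The power statement is correct for one mediator with standardised paths of 0.39. How far power falls in the joint models depends on correlations that the protocol does not give, so no single figure can replace it.

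**What to change.** 1. Do not enter the MSES-R total in a model that holds any of its subscales. If the total is wanted, run it in a separate model.
2. Delete the condition on significant group x time interactions, and fit the pre-specified mediators whatever their interaction result.
3. Use one mediator list per hypothesis, identical in Mediator hypotheses and Statistical analysis. Settle in particular MAIA for hypotheses 1 and 2, and NAS and Taking Responsibility for hypothesis 3. Which scales belong is for the investigators to decide.
4. In Sample size, restrict the mediation power wording to a single mediator with standardised paths of 0.39.

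No new data, visits or participants are needed. The price is that more mediators stay in each model, so intervals for individual effects will be somewhat wider, and the stated mediation power becomes less favourable.
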